## Abstract

**Introduction:**

A digital programme, MoodHwb, was codesigned with young people experiencing or at high risk of depression, parents/carers and professionals, to provide support for young people with their mood and well-being. A preliminary evaluation study provided support for the programme theory and found that MoodHwb was acceptable to use. This study aims to refine the programme based on user feedback, and to assess the acceptability and feasibility of the updated version and study methods.

**Methods and analysis:**

Initially, this study will refine MoodHwb with the involvement of young people, including in a pretrial acceptability phase. This will be followed by a multicentre feasibility randomised controlled trial comparing MoodHwb plus usual care with a digital information pack plus usual care. Up to 120 young people aged 13–19 years with symptoms of depression and their parents/carers will be recruited through schools, mental health services, youth services, charities and voluntary self-referral in Wales and Scotland. The primary outcomes are the feasibility and acceptability of the MoodHwb programme (including usage, design and content) and of trial methods (including recruitment and retention rates), assessed 2 months postrandomisation. Secondary outcomes include potential impact on domains including depression knowledge and stigma, help-seeking, well-being and depression and anxiety symptoms measured at 2 months postrandomisation.

**Ethics and dissemination:**

The pretrial acceptability phase was approved by the Cardiff University School of Medicine Research Ethics Committee (REC) and the University of Glasgow College of Medicine, Veterinary and Life Sciences REC. The trial was approved by Wales NHS REC 3 (21/WA/0205), the Health Research Authority(HRA), Health and Care Research Wales (HCRW), university health board Research and Development (R&D) departments in Wales, and schools in Wales and Scotland. Findings will be disseminated in peer-reviewed open-access journals, at conferences and meetings, and online to academic, clinical, and educational audiences and the wider public.

**Trial registration number:**

ISRCTN12437531.

STRENGTHS AND LIMITATIONS OF THIS STUDYMoodHwb was codesigned with young people with lived experience or at high risk of depression, parents/carers and practitioners.MoodHwb is bilingual, personalised according to user needs and preferences, and has been developed in line with evidence-based approaches to support young people with depressive symptoms and their parents/carers, friends and practitioners.Multiple methods will be used to collect data in a range of settings for the trial, including validated questionnaires, semistructured interviews, a focus group, and Web/app usage monitoring.As this is a feasibility study, we will not be able to determine the effectiveness of MoodHwb; however, the findings will inform the design of a definitive effectiveness trial.Participants will not be blind to treatment allocation as this is not possible with an intervention of this kind.

## Background

Depression is common in adolescence and is associated with social and educational impairments, deliberate self-harm and suicide. It can also mark the beginning of long-term mental health difficulties. Subthreshold depressive symptoms can also affect quality of life and are a risk indicator for depressive disorder. Early treatment and prevention of adolescent depression is, therefore, a major public health concern.^1 2^ There are also concerns about the economic burden of mental disorders.^3 4^ However, most adolescents with depression do not access or receive formal help and engaging young people (YP) in prevention and early intervention programmes is challenging.^5–7^

Guidelines for the prevention and management of depression in YP (eg, National Institute for Health and Care Excellence (NICE)^8^; American Academy of Child & Adolescent Psychiatry^9^) stress the need for good information and evidence-based psychosocial interventions for YP and families/carers, and digital interventions are recommended for mild depression in UK NICE guidelines.^8^ Digital mental health technologies (ie, resources and interventions) are a potential way of increasing access to support, at relatively low cost. Most YP in high-income countries have access to the internet and mobile devices, including in the UK.^10 11^ Many in low-income and middle-income countries can also access the internet, where there are few alternative sources of support.^12^ While there is increasing evidence for the effectiveness of technologies for adolescent depression,^13 14^ more programmes are needed to support adolescents that are accessible, evidence based, developed with user input and evaluated in line with research frameworks—and to provide greater options for YP in accessing help.^15^

MoodHwb is a bilingual (English and Welsh), interactive and multiplatform digital programme designed to support YP with their mood and well-being—and their families/carers, friends and practitioners (figure 1).

**Figure 1 F1:**
[figure not shown]
MoodHwb (v1) welcome screen (main image/left) and open menu (right) (from Bevan Jones *et al*^20^ 2020a).

It was codesigned using a series of interviews and focus groups with YP experiencing or at high risk of depressive symptoms (due to family history), parents/carers and professionals, alongside workshops with a digital media company and an animator.^16–18^ The development was also informed by a systematic review,^19^ design, educational and psychological theories, and a preliminary ‘logic model’ (programme theory) (figure 2).

**Figure 2 F2:**
[figure not shown]
Logic model for MoodHwb (above, from Bevan Jones *et al*^17^ 2018b), including potential pathways (below).

As part of the developmental work, there was an early evaluation of MoodHwb with a small number of YP and their parents/carers and practitioners, recruited via primary and secondary Child and Adolescent Mental Health Services (CAMHS), school counsellors and nurses, and a previous study sample (Early Prediction of Adolescent Depression (EPAD) study).^20^ Preliminary results were encouraging, and participants found the programme acceptable to use and gave feedback on how it could be improved. Findings also provided initial support for the programme theory, particularly regarding depression literacy, self-efficacy and depressive symptoms. In line with guidance for complex interventions, a larger feasibility trial is now required.^21 22^

The primary aims of the current study are to further refine and evaluate the feasibility, acceptability and potential impact of the digital programme MoodHwb and the feasibility and acceptability of the trial methods.

## Methods and analysis

### Initial development phase

The first phase involves the further refinement of the digital programme, based on the feedback provided by participants during the earlier evaluation. The key revisions recommended included improving the navigation, audiovisual and interactive elements, making it more personalised based on user preferences, developing the app version, and expanding the self-help and anxiety content.^20^ There were subsequent consultations with practitioners at the proposed trial recruitment centres across Wales and Scotland, and researchers in the field.

Regular updates are required to the design and content of digital programmes because of the fast-moving pace of the field and the emerging evidence and guidelines. We have completed reviews of the codesign of digital technologies with children and YP^18^ and technologies to support YP with depression and anxiety.^15^ The principal investigator (PI) has visited research centres in youth and digital mental health in New Zealand, Australia and the Republic of Georgia. Workshops and meetings will be held with the digital media company and animator that helped to develop the original prototype.

As part of a pretrial acceptability phase, YP in Wales and Scotland (n=10–15) will be given access to the new prototype. They will be recruited through school counsellors, charities, youth advisory groups (YAGs) and self-referrals. Adolescents will be eligible to take part if they are aged 13–19 years and have sufficient understanding of the English language, access to the internet and a valid email address. They will be interviewed to ensure that the changes made are acceptable ahead of the trial, and to explore issues of transferability in Scotland, given that the programme was developed in Wales. We will aim to recruit some YP who have experienced depressive symptoms. However, others with no experience of mental health difficulties will also give feedback, for example, on whether the programme is user-friendly and age-appropriate. Practitioners from health, education and youth services will be consulted further regarding the new prototype through meetings and online communication.

### Trial design

The feasibility study is a multicentre feasibility randomised controlled trial comparing the MoodHwb programme plus usual care (if the young person is receiving support) to digital information sheets on mood and well-being plus usual care (if receiving support) (figure 3). The research plan follows guidance for complex interventions,^21 22^ and digital person-centred interventions.^23^

**Figure 3 F3:**
[figure not shown]
Participant flow diagram. NB: Web/app usage data of those in the intervention arm will be collected for 6 months after baseline.

### Setting and participants

Trial participants will be identified by practitioners in schools (by eg, counsellors, nurses, teachers), mental health centres (mainly primary services), charities, youth services and sports academies in Wales, and in schools and charities via the second site at the University of Glasgow, Scotland. The School Health Research Network (SHRN, Wales) and Schools Health and Well-being Improvement Research Network (SHINE, Scotland) will be involved. These sources were chosen as the developmental work suggested that the most appropriate setting for the programme would be the time when depressive difficulties start and YP first present—and it is therefore a form of early intervention.^17 20^ We will also recruit self-referrals, for example, through social media and online advertising, including through the National Centre for Mental Health (NCMH), Wolfson Centre for YP’s Mental Health (WCYPMH) and TRIUMPH youth mental health network.

YP will be eligible if they: (1) are aged 13–19 years, (2) are experiencing depressive symptoms, (3) have a sufficient understanding of English to complete outcomes measures, (4) have access to the internet and a valid email address and (5) live in Wales or Scotland. Exclusion criteria are: (1) already receiving specialist treatment for depression (eg, cognitive behavioural therapy (CBT) in secondary CAMHS) and (2) the presence of other mental health difficulties where alternative support might be appropriate. Parents and carers will be targeted for the trial if they have an adolescent with depressive symptoms. Professionals will be approached if they work with YP who present with mental health difficulties.

### Sample size

We aim to recruit up to 120 adolescent participants and their parents/carers. Approximately two-thirds of the participants will be from Wales and one-third from Scotland. We expect a dropout of around 30%, based on previous digital health studies and the development and early evaluation work. With a sample size of 120 we can estimate the overall expected retention rate of 0.7 to within ±0.082 (70%±8.2%).

### Recruitment

School, mental health, youth, or charity practitioners will identify potentially eligible YP and ask them whether they are interested in participating. The practitioners will provide a study postcard which directs the YP to the bilingual study website (www.ncmh.info/digital-support-study/), where there will be details of the study and information sheets. We will ask practitioners to keep a screening log of all YP approached. There will be a link to the website via social media and online advertisements for self-referrals.

If they are interested in taking part, YP will be asked to complete an online eligibility form on the website. This will include questions on their contact details and to assess whether they meet the eligibility criteria, including items from the Mood and Feelings Questionnaire (MFQ)^24^ to measure depressive symptoms. They would be eligible if they score 20 or over on the MFQ. If they score 29 or over, they would also be advised to seek help and we will contact their general practitioner (GP), as this indicates a ‘major depressive disorder’.^25^ They will not be eligible if they access specialist treatment (eg, CBT; see exclusion criteria). The MFQ is commonly used in clinical and research practice and is a recommended screening tool in NICE guidelines for depression in children and YP.^8^ The questionnaire and these cut-offs have also been used in previous trials of digital interventions for depression in YP.^26 27^ The research team will then contact those who are interested to discuss the project (including consent forms and questionnaires), confirm their eligibility, respond to their questions and ask whether their parents/carers are interested in participating.

### Consent

Online consent forms are provided for the participants to complete, before completion of baseline questionnaires. If under 16 years old, YP will be asked to provide assent while their parent or legal guardian will be asked for consent. Dual consent and assent will be required for participation. Those aged 16 years or older will be able to provide their own consent. Parents/guardians and professionals who participate will also be asked to complete consent forms.

### Randomisation

Participants will be randomised at a 2:1 ratio to either the digital programme, MoodHwb plus usual care, or digital information sheets on mood and well-being in YP plus usual care (figure 3). We decided to randomise at a 2:1 ratio to allow for more information to be gained about those receiving the intervention. The permuted block randomisation will be computerised and stratified according to site (Wales and Scotland). This will be built into the study database overseen by the Centre for Trials Research (CTR, Cardiff University), providing remote access and preserving allocation concealment. Because of the nature of the intervention, participants will not be blind to their allocation, however, data analysis will be carried out blind to allocation.

### Intervention

MoodHwb is a digital programme to support YP with their mood and well-being, particularly those with elevated depressive symptoms. It can also be used by their families/carers, friends and practitioners. The programme and development process are described in detail in previous publications.^16–18^

It is designed to engage YP by using developmentally appropriate language, illustrations, animations and interactive components. It aims to promote self-help, help-seeking where appropriate and social support. While it was founded primarily on psychoeducation, it also includes elements of CBT, behavioural activation, positive psychology, and interpersonal, family systems and behaviour change theories. The first version was developed primarily as a website, although the interactive sections (eg, mood diary) are also available in an ‘app’. It could be used independently as a ‘standalone’ programme by YP (or parents/carers, friends or professionals) or supported by another person.

From the welcome screen, the user is asked questions (eg, regarding their mood and anxiety levels), and the answers (1) are stored in their ‘profile’ section and (2) help to signpost to the relevant subsections on the subsequent ‘dashboard’ screen, therefore, personalising the content. Along with this ‘mood diary’, there are other interactive elements: a goal-setting element and a section to save links to helpful resources. Five sections were developed for YP (figure 1), and these cover: (1) low mood and depression, (2) possible reasons, (3) self-help approaches, (4) sources of help and (5) associated health difficulties. There is a sixth section to support those who might be concerned about YP, such as parents/carers, friends and practitioners. It is recommended that users navigate sections in this order, but they can use it in any way that is helpful for them. Each of these sections includes information, animations, personal stories, exercises and links to relevant resources. MoodHwb is bilingual—‘hwb’ is the Welsh translation for ‘hub’, and can mean a ‘lift’ or ‘boost’. HwbHwyliau is the Welsh name for the programme.

Participants in the control arm will be emailed a digital information pack, which will consist of digital information sheets on mood and well-being (including depression) from the NCMH, Royal College of Psychiatrists and YoungMinds websites. Such resources offer general information, are widely accessible online, and have been used by control arm participants in similar trials.^27^

### Patient and public involvement

The programme was codesigned using a series of interviews (n=12) and focus groups (n=6) with (1) YP who either had a history of depression or were at elevated risk, (2) parents/carers and (3) professionals. Participants were recruited from CAMHS in Wales, and families from the EPAD study. As noted, further feedback on the programme was provided during the early evaluation.^20^

The project has been adopted by the Centre for Development, Evaluation, Complexity and Implementation in Public Health Improvement (DECIPHer, Cardiff University), and the study plans were developed in collaboration with their YAG, ALPHA (Advice Leading to Public Health Advancement). We will collaborate further with them as well as the YAGs of the WCYPMH, NCMH and TRIUMPH network. A young person has been invited to join the trial steering committee (TSC), and other YP (aged 13–16 years) have reviewed study documents, for example, information sheets and consent forms. Practitioners and researchers have been consulted regarding the plans.

### Assessment schedule

Data will be collected at (1) baseline and (2) follow-up, 2 months after randomisation. Data will be collected from (1) baseline and follow-up online questionnaires; (2) semistructured interviews with YP and parents/carers who used the programme; (3) a focus group with professionals and (4) Web/app usage data (table 1).

**Table 1 T1:** Schedule of enrolment, interventions and assessments for the trial

Time point	Screening (contact 1)	Baseline (contact 1)		Month 2 (contact 2)	
Activity		Intervention	Control	Intervention	Control
Referral to the trial/register of interest	X				
Eligibility assessment	X				
Consent process	X				
Randomisation	X				
Access to MoodHwb		X			
Questionnaires					
Adolescent Depression Knowledge Questionnaire^34^		·/○	·/○	·/○	·/○
Depression Stigma Scale^35^		·/○	·/○	·/○	·/○
General Self-Efficacy Scale^36^		·	·	·	·
General Health-Seeking Questionnaire^37^		·	·	·	·
Warwick-Edinburgh Mental Well-being Scale^31^		·/○	·/○	·/○	·/○
Mood and Feelings Questionnaire^24^		·/○	·/○	·/○	·/○
Revised Children’s Anxiety and Depression Scale-Short Version-25^38^		·/○	·/○	·/○	·/○
Hospital Anxiety and Depression Scale^39^		○	○	○	○
Items on health economics and life events^40^		·/○	·/○	·/○	·/○
Items on use and acceptability of MoodHwb				·/○	
Process evaluation					
Young person interview (n=20–25)				·	
Parent/carer interview (n=10–15)				○	
Professionals focus group				*	

(·Participant/○ parent/*professionals) ‘contact’ will comprise phone/videoconferencing discussion and completion of online forms/questionnaires.

We will use remote methods for recruitment, consent and data collection (eg, phone, email, videoconferencing, online forms and questionnaires) because these have been shown to be efficient and effective ways of conducting research during the COVID-19 pandemic. This approach is consistent with the digital nature of the programme and would enable us to reach more YP. All participants will be offered £10 gift vouchers after (1) completing baseline questionnaires, (2) completing follow-up questionnaires and (3) participating in interviews.

#### Baseline

At baseline, YP in both arms will complete questionnaires which will include items on their demographic and contact information, health and use of services, and standardised questionnaires on knowledge, stigma, self-efficacy, help-seeking, well-being, symptoms and life stresses (table 1). The parent/carer questionnaires will include items on the young person’s details, use of services and symptoms, and their knowledge, beliefs, well-being, and symptoms. All participants will also complete items on the acceptability of the questionnaires.

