#### Quantitative analysis

Baseline questionnaire data will be scored according to the validated scoring algorithms from the relevant literature. Missing item-by-item data will be handled according to the scoring algorithm for each measure individually. Baseline scores will be presented descriptively, using summary statistics (means, SD, medians, IQR and percentages with associated 95% CI where appropriate) for the whole group and by arm. Distributional assumptions will be checked, and data transformation carried out if required. A comparison of randomised groups will be tabulated but not tested, in line with the feasibility aims. A comparison of baseline data for those completing and not completing the study will be tabulated to assess drop-out bias.

Scores at the 2-month time point will be tabulated and compared in a complete case analysis. No hypothesis tests will be carried out but 95% CI for the difference at 2 months between the two arms will be estimated and reported. These will be adjusted for baseline score and any factors such as site used to balance the randomisation. Statistical analysis will be performed using Stata software (version 17), but no p values will be presented. We will further develop and test the MoodHwb logic model (figure 2) using multiple methods, and examine possible mechanisms of action and active components. This will help to define a core set of outcome measures (related to the model) and identify the most appropriate primary outcome for evaluation in an effectiveness trial.

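### Table 1 schedules randomisation before the baseline questionnaires, so allocation could influence the self-reported scores used to adjust the 2-month differences

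*Protocol article*

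**What the plan says.** All references are to the protocol article.

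- **Assessment schedule, Table 1** ("Schedule of enrolment, interventions and assessments for the trial"). The randomisation row has one mark, in the Screening column, below the rows for referral, eligibility and consent. All the first-round questionnaires are in the following Baseline column, which is split into Intervention and Control. Access to MoodHwb is marked in that column too, under Intervention. The two column headings begin "Screening (contact 1" and "Baseline (contact 1", so both steps belong to the same contact.
- **Baseline.** "At baseline, YP in both arms will complete questionnaires".
- **Consent.** "Online consent forms are provided for the participants to complete, before completion of baseline questionnaires". This orders consent and questionnaires. It does not place randomisation relative to either.
- **Randomisation.** "participants will not be blind to their allocation, however, data analysis will be carried out blind to allocation". Site is the only stratification factor, so nothing on the baseline form is needed in order to allocate.
- **Quantitative analysis.** For the confidence intervals on the 2-month between-arm differences: "These will be adjusted for baseline score and any factors such as site used to balance the randomisation".

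**The concern.** Adjusting for a baseline score is safe because treatment assignment cannot have affected something measured before it. If the questionnaire is answered after allocation, that guarantee is lost.

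The measures are online self-reports of knowledge, stigma, self-efficacy, help-seeking, well-being and symptoms. A young person who has just learned that they will get the information pack, or the programme, may answer some of these differently. Since access to MoodHwb is tabulated in the same column as the questionnaires, some exposure before completion is not ruled out either, and knowledge and stigma are among the things the programme is meant to change. Analysing the data blind does not help, because the influence would already be in the recorded answers.

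At stake are the baseline-adjusted differences at 2 months. They are secondary and untested, but they are meant to help choose the primary outcome of a definitive trial. A feasibility trial also tests the procedures that the later trial would inherit.

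**Working it through.** **1. The plan's own figure.** The only computed design figure is the precision of the retention rate (Sample size): 1.96 × √(0.7 × 0.3 / 120) = 0.082. It reproduces the stated ±0.082 and does not depend on the order of events discussed here.

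**2. The order of events.** Table 1 is the only place in the available text that positions randomisation relative to the baseline questionnaires, and it positions it earlier. Consent places only consent before the questionnaires. Randomisation says that participants are unblinded but not when they learn their arm. The Baseline section's reference to both arms is compatible with the tabulated order. It could equally be written in retrospect of a trial that collects baseline first, so Table 1 carries the point.

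**3. Size of the possible bias.** Let d be the shift in reported baseline score that knowledge of allocation causes (intervention minus control, in SD units). Let b be the slope of follow-up on baseline. If the shift affects the baseline report only, the adjusted difference is biased by

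bias = −b × d.

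The protocol gives neither b nor d, so both are assumptions: b = 0.5 to 0.7 and d = 0.1 to 0.3 in absolute size.

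| | d = 0.1 | d = 0.2 | d = 0.3 |
|---|---|---|---|
| b = 0.5 | 0.05 | 0.10 | 0.15 |
| b = 0.6 | 0.06 | 0.12 | 0.18 |
| b = 0.7 | 0.07 | 0.14 | 0.21 |

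Entries are absolute values in SD; the sign is opposite to that of d. If controls report baseline scores that are too high, for instance, the adjusted difference is pushed upwards.

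A simulation agrees. With no true effect, 56 and 28 completers, b = 0.6 and the control baseline raised by 0.2 SD (d = −0.2), the mean estimate over 4,000 runs was 0.12 SD. The formula gives −0.6 × (−0.2) = 0.12.

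**4. Comparison with random error.** With 120 participants at 2:1 the arms are 80 and 40. At 30% dropout, taken as equal in both arms, 56 and 28 complete. With an assumed baseline correlation of 0.5, the 95% half-width is

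1.96 × √(1/56 + 1/28) × √(1 − 0.5²) = 0.39 SD.

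For correlations from 0.4 to 0.7 it runs from 0.42 down to 0.32 SD. The largest bias in the table, at b = 0.7, is 0.21 SD against a half-width of 0.32 SD at a correlation of 0.7.

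**The case against.** The strongest reply is that the order is inferred from a table layout. Screening and Baseline share one contact, the rows are grouped by type of activity, and the split by arm may only show who completes which form. Unblinded does not mean informed before answering: allocation could be generated and then disclosed after the forms. The flow diagram (Figure 3) is not shown in the text available here and might settle the order. An article also commonly leaves the database trigger to the full protocol.

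Most of this stands as a limit on the claim. It does not remove the claim. Table 1 is an explicit schedule, not an omission, and no available text corrects it. If it is merely mis-drawn, it still needs correcting.

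The reply is also right about scale. The shifts are assumed, the bias would be smaller than the random error, and the affected scores are secondary, with no hypothesis tests and no claim about effectiveness.

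A reader might infer more than the documents support:

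- **That participants do answer knowing their arm.** The time of disclosure is not stated.
- **That every between-arm estimate is biased.** Only baseline-adjusted estimates are exposed, and only on scales where the report shifts by arm.
- **That the retention rate is damaged.** Losses after randomisation but before baseline are legitimate retention information, and the planned precision concerns the overall rate.
- **That slow baseline completers get less than 2 months of access.** This needs access to wait for baseline completion, which the text does not say. For any one participant it also conflicts with the worry that access comes before the questionnaires.

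**Conclusion.** The point holds in a limited form. Followed as tabulated, the schedule lets allocation influence a covariate that the analysis then adjusts for, and no available text prevents it. Under the assumed slopes and shifts the bias is 0.05–0.21 SD in absolute size, against a half-width of about 0.39 SD at a baseline correlation of 0.5. It is smaller than the random error, but the interval would not reflect it and a larger sample would not reduce it.

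This rests on three things: that Table 1 describes the real order, that allocation is known when the forms are answered, and that the answers then shift by arm. The first is what the document shows; the other two are possible but not stated. With one contact covering both steps, the interval may be short. The consequence is confined to secondary, descriptive estimates.

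**What to change.** 1. In Table 1, place randomisation after the baseline questionnaires, and say in the text that these are completed before allocation is made or disclosed.
2. Have the study database allow allocation, and release of the MoodHwb log-in or the information pack, only once the baseline form has been submitted.
3. For participants already randomised (Trial status gives a recruitment start of November 2022), record the date and time of baseline completion relative to allocation. Repeat the adjusted estimates without those who completed it afterwards. This is a sensitivity check only: it selects on an event after randomisation, and few participants may remain if the tabulated order was followed.
4. For depressive symptoms, the eligibility form already collects MFQ items (Recruitment). If they can be scored, they offer a covariate measured before allocation.

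The cost is one validation rule in a database that already performs the randomisation, and a corrected table. The shared contact should make the reordering easy. The downside is that slightly fewer people reach randomisation, because those who do not complete baseline leave first; that is the preferable point at which to lose them.
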